## Abstract

**Background:**

Community-acquired pneumonia (CAP) causes a large burden of disease. Due to difficulties in obtaining representative respiratory samples and insensitive standard microbiological methods, the microbiological aetiology of CAP is difficult to ascertain. With a few exceptions, standard-of-care diagnostics are too slow to influence initial decisions on antimicrobial therapy. The management of CAP is therefore largely based on empirical treatment guidelines. Empiric antimicrobial therapy is often initiated in the primary care setting, affecting diagnostic tests based on conventional bacterial culture in hospitalized patients. Implementing rapid molecular testing may improve both the proportion of positive tests and the time it takes to obtain test results. Both measures are important for initiation of pathogen-targeted antibiotics, involving rapid de-escalation or escalation of treatment, which may improve antimicrobial stewardship and potentially patient outcome.

**Methods:**

Patients presenting to the emergency department of Haukeland University Hospital (HUH) in Bergen, Norway, will be screened for inclusion into a pragmatic randomised controlled trial (RCT). Eligible patients with a suspicion of CAP will be included and randomised to receive either standard-of-care methods (standard microbiological testing) or standard-of-care methods in addition to testing by the rapid and comprehensive real-time multiplex PCR panel, the BioFire® FilmArray® Pneumonia Panel *plus* (FAP *plus*) (bioMérieux S.A., Marcy-l’Etoile, France). The results of the FAP *plus* will be communicated directly to the treating staff within ~2 h of sampling.

**Discussion:**

We will examine if rapid use of FAP *plus* panel in hospitalized patients with suspected CAP can improve both the time to and the proportion of patients receiving pathogen-directed treatment, thereby shortening the exposure to unnecessary antibiotics and the length of hospital admission, compared to the standard-of-care arm. The pragmatic design together with broad inclusion criteria and a straightforward intervention could make our results generalizable to other similar centres.

**Trial registration:**

ClinicalTrials.govNCT04660084. Registered on December 9, 2020

**Supplementary Information:**

The online version contains supplementary material available at 10.1186/s13063-022-06467-7.

## Administrative information

Note: the numbers in curly brackets in this protocol refer to SPIRIT checklist item numbers. The order of the items has been modified to group similar items (see http://www.equator-network.org/reporting-guidelines/spirit-2013-statement-defining-standard-protocol-items-for-clinical-trials/).

## Introduction

### Background and rationale {6a}

Lower respiratory tract infections, including community-acquired pneumonia (CAP), are a leading cause of hospital admissions and mortality in all age groups [1–5]. Pneumonia places a large burden on healthcare resources, with associated enormous annual costs in Europe, mainly due to hospitalization and absence from work [6].

Pneumonia is an infection of the lungs, with accompanying inflammation. Typical clinical symptoms include cough with or without sputum, fever, dyspnoea and chest pain [7]. However, elderly patients, who represent most admissions for pneumonia, present without many of these features. Moreover, chest radiography is hampered by suboptimal sensitivity to detect pulmonary infiltrates, especially in the initial phase of the disease and in elderly patients [8–10]. In light of the diagnostic difficulties, the reported incidence of hospital-treated CAP varies considerably: between 10 and 420 cases per 10,000 adults per year in developed countries, with higher numbers in children and elderly [11–13]. Similarly, estimated mortality rates are between 1 and 48% and consistently found to increase with age [5, 11]. A prospective study conducted at Drammen Hospital, Norway, found that 1- and 5-year mortality rates were 8.9% and 27.1%, respectively, among hospitalized CAP patients [14].

As CAP is a potentially serious infection, antibiotics are often given rapidly after presentation to hospital. Due to uncertain microbial aetiology, patients are initially treated with empirical antibiotics that cover a broad range of potential pathogens. The microbiological aetiology of CAP based on conventional routine microbiological testing is achieved in up to 30–40% of cases [12, 15]. With a few exceptions, standard-of-care diagnostic methods are too slow to influence early decisions on antimicrobial therapy. Culture-based techniques are also affected by prior use of antibiotics. Furthermore, sampling from the lower respiratory tract is problematic due to contamination and colonization from the upper respiratory tract flora. The management of CAP therefore largely relies on national empirical treatment guidelines that reflect the prevailing local epidemiology and microbial resistance profiles. Improving microbiological identification and enhancing rapid detection of significant pathogens could have a major impact on the decision-making process, by providing real-time information for treatment decisions within the emergency department. Rapid molecular testing for CAP aetiology may facilitate pathogen-directed treatment, reduce unnecessary antibiotic use, shorten length of hospital stay, improve viral detections and treatment and rationalize isolation facility use. However, limited evidence exists to support its use over standard-of-care microbiological testing. A recent randomised controlled trial (RCT) evaluated the use of molecular testing for respiratory viruses in hospitalized CAP patients in UK [16]. Molecular testing was associated with a greater proportion of patients being treated with brief courses of antibiotics, improved antiviral use, reduced length of stay and was considered safe. Moreover, respiratory viruses were detectable in up to 45% of hospitalized adults with acute respiratory illness [16]. These findings need confirming in other studies that include rapid molecular tests, targeting both viral and bacterial pathogens and with alternate outcome measures.

Tests using multiplex real-time polymerase chain reaction (PCR) can reduce the time to results compared with standard PCR panels from 12 to 48 h to about 2 h, with the potential to direct initial antimicrobial choice. The new generation BioFire® FilmArray® Pneumonia Panel *plus* (FAP *plus*) (bioMérieux S.A., Marcy-l’Etoile, France) includes the automated detection of 27 relevant bacterial (including atypical bacteria) and viral respiratory pathogens together with seven antimicrobial resistance genes [17]. The assay requires a 2-min hands-on time and a run time of about 1 h. We hypothesize that utilizing the FAP *plus* panel in CAP patients can improve both the time to and the proportion of patients receiving pathogen-directed treatment, thereby shortening the exposure to unnecessary antibiotics and the length of hospital admission.

### Hypotheses {7}

CAPNOR will assess the impact of a rapid molecular diagnostic approach (FAP *plus*) in adult CAP patients presenting to the emergency department, compared to the current standard-of-care microbiological testing. We hypothesize that the FAP *plus* may lead to an increase in the proportion of patients treated with, and shorten the time to, pathogen-directed treatment of CAP and so will reduce unnecessary use of broad-spectrum antibiotics for treatment of CAP.

### Trial design {8}

CAPNOR is a single-centre, single-blind, parallel-arm randomised controlled superiority trial. In an allocation ratio of 1:1, eligible patients will be randomised to receive either standard-of-care methods (standard microbiological testing) or standard-of-care methods in addition to testing by the FAP *plus*. The trial is pragmatic with a PRECIS-2 rating of the nine domains as follows: eligibility: 4, recruitment: 5, setting: 5, organization: 5, flexibility (delivery): 4, flexibility (adherence): 5, follow-up: 5, primary outcome: 5, primary analysis: 5 [18].

### Feasibility

To inform the trial, a prospective cohort feasibility study was carried out with 104 patients with suspected CAP [19]. The feasibility study mirrored the procedures described in the full-scale trial but without randomised of respiratory samples into two treatment arms. All lower respiratory tract samples were tested both by standard microbiological testing and by the FAP *plus*. The feasibility study was used to assess several parameters including the feasibility of recruitment, the included clinical and laboratory procedures and the usability and efficiency of the data entry process, data transfer and data analysis using the study-specific electronic case report form (eCRF) provided by Viedoc (Viedoc Technologies, Uppsala, Sweden). Thus, the feasibility study informed on any procedural or design refinements that were needed for the ensuing full-scale trial. Results from the feasibility study are reported elsewhere [19].

## Methods: participants, interventions and outcomes

### Study setting {9}

Over the 3-year period 2020–2023, CAP patients admitted to Haukeland University Hospital in Bergen, Western Norway, will be screened for inclusion into the CAPNOR study. HUH is a large academic hospital that serves as a local hospital for a population of approximately 470,000 persons and functions as a referral hospital for approximately 1,000,000 inhabitants. At admission, eligible patients with a suspicion of CAP will be recruited in the emergency department at HUH.

### Eligibility criteria {10}

#### Inclusion criteria

Adults (aged ≥18 years) presenting to the emergency department with a suspicion of CAP and fulfilling at least two of the following criteria: new or worsening cough, new or worsening expectoration of sputum, new or worsening dyspnoea, hemoptysis, pleuritic chest pain, radiological evidence of pneumonia, abnormalities on chest auscultation and/or percussion, and fever (≥38.0°C).

Written informed consent is needed from the patient or from their legal guardian/close relative at the time of recruitment.

#### Exclusion criteria

Any of the following conditions prohibit participation in the trial:Severe bronchiectasis (defined as patients in need of regular follow-up and treatment by a pulmonologist due to bronchiectasis)Cystic fibrosisA palliative approach (defined as life expectancy below 2 weeks)Hospitalization within the last 14 days prior to admissionPatients not willing or able to provide a lower respiratory tract sample at admission

### Who will take informed consent? {26a}

The study physicians or study nurses will brief patients or the patient’s legally authorized representative, with regard to the nature of the study. Patients will be informed that their participation is voluntary and will receive information sheets. Patients or their legally authorized representative(s) will be required to sign a statement in an informed consent form (ICF) that meets the requirements of the Regional Committee for Medical and Health Research Ethics in Norway (REC), and this will be documented in the study eCRF. A copy of the ICF will be provided to the patient or the patient’s legally authorized representative. The ICF will contain a separate section that addresses the use of remaining mandatory samples for exploratory research. Patients are informed that they are free to refuse to participate and may withdraw their consent at any time and for any reason during the storage period of clinical samples.

### Additional consent provisions for collection and use of participant data and biological specimens {26b}

Patients are informed about the storage and use of their data and biological samples for future research on CAP. Informed consent is procured prior to collection of participant data and biological specimens. All biological specimens will be destroyed 5 years after the project ends.

## Interventions

### Explanation for the choice of comparators {6b}

The trial compares two types of microbiological testing approaches for the assessment of microbiological aetiology in CAP patients. The impact of novel rapid testing by the FAP *plus* is evaluated against standard microbiological testing (standard-of-care), which is the comparator arm.

### Intervention description {11a}

The trial evaluates the utility of diagnostic tests used for diagnosing the microbiological aetiology in CAP. Blood tests and cultures, urine sample for urine antigen tests, chest x-ray and samples from the respiratory tract are collected in all patients following inclusion. Due to local infection control measures, the patients’ SARS-CoV-2 status needs to be clarified before collecting samples from the lower respiratory tract. Following consent, all patients are tested for their SARS-CoV-2 status. A confirmed case of SARS-CoV-2 is defined as a positive result on the rapid XpertXpress SARS-CoV-2 or SARS-CoV-2/FLU/RSV test run on the GeneXpert system (Cepheid, Sunnyvale, U.A.) or on Cobas SARS- CoV-2 & Influenza A/B test run by the Cobas Liat System (Roche Molecular Systems, Inc., Pleasanton, CA) using naso-/oropharyngeal swab samples. Lower respiratory tract samples are collected after sputum induction or by endotracheal aspiration in both arms. On receipt of the lower respiratory tract sample at the Department of Microbiology, the patients are randomised to the following arms:

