### Participant timeline {13}

The participant timeline is shown in Fig. 1. A schematic diagram with the time schedules for enrolment, interventions and assessments for participants is shown in Fig. 2. Eligible patients are identified and included in the emergency department. Due to local infection control regulations, the patient’s SARS-CoV-2 status is clarified before collection of lower respiratory tract samples. Following consent, all suspected CAP patients are tested for SARS-CoV-2 by naso- and oropharyngeal swab samples. In both SARS-CoV-2- negative and SARS-CoV-2-positive patients, collection of lower respiratory tract samples is performed as soon as possible in the emergency department, either by induced sputum or by endotracheal aspiration. Spontaneous sputum is collected as an exception if an induced sputum cannot be collected. If sputum induction is unsuccessful, endotracheal aspiration is performed. Respiratory tract samples are sent immediately via a pipeline system to the Department of Microbiology at HUH, where microbiological testing takes place. In patients randomised to the FAP *plus*, the test result is phoned to the treating staff.

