## Data collection and management

### Plans for assessment and collection of outcomes {18a}

Baseline information is collected by study nurses or investigating physicians through a structured interview in the emergency department. Symptoms and findings upon clinical examinations are recorded. Data pertaining to antimicrobial treatment and decisions, results from laboratory tests and medical imaging are obtained from electronic medical records and charts, after patient discharge, and used for the evaluation of the primary outcomes. For each patient, two experienced physicians separately evaluate the clinical relevance of all microbiological findings [19] and determine if and when the patient received pathogen-directed antimicrobial treatment based on a microbiological test result. In case of any inconsistency between the two physicians, a third independent physician will arbitrate. To be considered as pathogen-directed treatment, study physicians will note if (a) there is a change in antimicrobial treatment based on a microbiology test result or (b) a continuation of already correctly initiated antimicrobial treatment based on a microbiology test result, and (c) discontinuation of antimicrobial treatment based on negative microbiological test result(s). Empirical and pathogen-directed therapy will be determined using national guidelines recommended by the Norwegian Directorate of Health, data from national susceptibility reports, as well as results from anti-microbial susceptibility testing provided by the Department of Microbiology, HUH, as appropriate [25, 26]. Data will be registered in our eCRF (Viedoc). Data for the 30- and 90-day mortality, and 1- and 5-year mortality will be obtained from the Norwegian Cause of Death Registry.

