## Statistical methods

### Statistical methods for primary and secondary outcomes {20a}

For the first primary outcome, which is a binary outcome capturing whether or not provision of pathogen-directed treatment was given, the comparison between arms will be performed using a logistic regression model. The difference between arms will be quantified by means of an odds ratio or as a difference in probabilities (“a risk difference”). For the second primary outcome, which is a quantitative outcome subject to right censoring capturing the time to pathogen-directed treatment was given, the comparison between arms will be carried out using a semi-parametric or fully parametric event-time model such as the Cox proportional hazards model or accelerated failure time model. Relevant covariate adjustment, including age and sex, will be included in both models.

Secondary outcomes will be analysed using the same two types of models as used for the two primary outcomes. However, for some quantitative secondary outcomes, there will be no right censoring present and, in such cases, linear models or linear mixed models will be fitted, depending on the absence or presence of repeated measurements.

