## Discussion

The COVID-19 pandemic spread to Norway during March 2020 and forced us to adapt to new routines and infection control measures deployed at hospitals and in the society at large. The planned start of the trial was therefore delayed with about 6 months. The time available to collect data and complete inclusions at the emergency department was initially restricted due to shortage of isolation facilities and a large inflow of patients. Initially, each patient is screened for SARS-CoV-2 before an induced sputum sample can be collected at the emergency department, with the subsequent risk of delaying the lower respiratory tract sampling. This is minimized by rapidly sending an oro- or nasopharyngeal swab for analysis by a rapid SARS-CoV-2 test, which provides results within 1 h.

With the national infection control measures, including social distancing, use of facemasks and home office solutions, the number of hospital admissions for lower respiratory tract infections at Bergen Health Trust fell during the first year of the pandemic [24]. This has resulted in slower inclusion rates than anticipated. Finally, COVID-19 and related quarantine among study staff has led to problems with optimal recruitment and timely pursuit of pre-defined study milestones due to absenteeism.

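### A rapid viral result known before randomisation can drive both primary outcomes in either arm, yet it is not a named covariate and treatment directed before time zero has no scoring rule

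*Protocol article*

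**What the plan says.** **Order of events.** Under Intervention description {11a}, "Following consent, all patients are tested for their SARS-CoV-2 status". The assays listed there include "the rapid XpertXpress SARS-CoV-2 or SARS-CoV-2/FLU/RSV test run on the GeneXpert system" and a Cobas Liat test that also covers influenza A/B. Participant timeline {13} says "SARS-CoV-2 status is clarified before collection of lower respiratory tract samples", and the Discussion describes a "rapid SARS-CoV-2 test, which provides results within 1 h". Randomisation follows: "On receipt of the lower respiratory tract sample at the Department of Microbiology, the patients are randomised to the following arms".

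**Who stays in.** A positive swab is not among the exclusion criteria. Participant timeline {13} covers negative patients in the same sentence as "SARS-CoV-2-positive patients, collection of lower respiratory tract samples is performed as soon as possible in the emergency department". The standard-of-care section has positive SARS-CoV-2 results phoned to the treating staff, and the FAP plus arm receives all standard tests as well.

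**What counts.** Outcomes {12} defines both primary outcomes through treatment based on a clinically relevant microbiological result. The clock starts at receipt of the respiratory samples and runs for 48 h. Under {18a}, two physicians review all microbiological findings and "determine if and when the patient received pathogen-directed antimicrobial treatment based on a microbiological test result". A change of treatment, continuation of treatment already correctly started, or discontinuation on negative results can each qualify.

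**Analysis.** Section {20a} plans logistic regression for the binary outcome and a Cox or accelerated failure time model for the time outcome: "Relevant covariate adjustment, including age and sex, will be included in both models". Section {20c} analyses all randomised patients.

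**The concern.** The rapid result is normally a baseline variable: it is known before allocation and is plausibly related to the outcome. Nothing in the primary outcome definitions separates treatment directed by it from treatment directed by later results. Two consequences follow.

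1. **Sensitivity.** An event settled by a result already on the chart cannot be changed by allocation. It occurs equally often in both arms in expectation, and it adds either dilution or removable variance.
2. **Time zero.** The second primary outcome starts at sample receipt and provides only for right censoring. Because continuation of earlier treatment can qualify, some patients may meet the definition before the clock starts. A negative time has no risk set in a Cox model, and an accelerated failure time model on log time cannot take zero or negative values. Dropping these patients would conflict with analysing everyone randomised, and recoding them needs a rule. Section {17a} says that outcome assessors and statisticians are not blinded, so that rule should not be chosen once allocation is known.

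**Working it through.** **Inputs from Sample size {14}:** 40% versus 50%; significance level 0.025 per outcome (taken as two-sided, since sidedness is not stated); power 0.8; 470 per arm for the binary outcome; 0.2 SD and 477 per arm for the time outcome. **Assumed:** the share q of patients with an event fixed by the rapid result. The documents give no figure; 10% and 20% are used as illustrations.

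**Reproducing the plan.** With z = 2.2414 and 0.8416 and a pooled test:

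- Binary: n = [2.2414·√(2·0.45·0.55) + 0.8416·√(0.24 + 0.25)]² / 0.10² = 469.2, so 470 per arm, as stated.
- Time: n = 2·(2.2414 + 0.8416)² / 0.2² = 475.3, so 476, against 477 stated.
- Dropout: 940/0.9 = 1044.4, so 1045; 954/0.9 = 1060. Both as stated.

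The binary outcome at 477 per arm, using power = Φ{[√n·|p₂ − p₁| − 2.2414·√(2p̄(1 − p̄))] / √(p₁(1 − p₁) + p₂(1 − p₂))}, has power 0.807.

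**Case A: the 40% and 50% already include these events.** The 10-point difference and the 81% power are unchanged. If every rapid-positive patient has the event, positives add no information and adjustment amounts to comparing the negatives:

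- q = 10%: (0.40 − 0.10)/0.90 = 33.3% versus (0.50 − 0.10)/0.90 = 44.4%, with 429.3 per arm: power 0.865.
- q = 20%: (0.40 − 0.20)/0.80 = 25.0% versus (0.50 − 0.20)/0.80 = 37.5%, with 381.6 per arm: power 0.933.

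These are upper limits. Suppose instead that 10% or 20% are positive and only 80% of them have the event in each arm. The negatives then have (0.40 − 0.08)/0.90 = 35.6% versus (0.50 − 0.08)/0.90 = 46.7%, or (0.40 − 0.16)/0.80 = 30.0% versus (0.50 − 0.16)/0.80 = 42.5%. A risk difference standardised over the two strata keeps the 10 points. Its variance is the stratum-share-weighted sum of the within-stratum variances divided by 477. Power is 0.83 and 0.86.

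**Case B: these events come on top of 40% and 50%.** Each arm's rate is q + (1 − q)p, so the difference is 10·(1 − q) points:

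| q | Rates | Power, unadjusted | Power, adjusted (at most) |
|---|---|---|---|
| 10% | 46.0% v 55.0% | 0.706 | 0.760 |
| 20% | 52.0% v 60.0% | 0.598 | 0.705 |

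The adjusted column is 40% versus 50% in the 477·(1 − q) negatives. For the time outcome, shrinking 0.2 SD to 0.2·(1 − q) SD gives unadjusted power of 0.705 at q = 10% and 0.591 at q = 20%.

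**The case against.** **A reader might infer bias.** The documents do not support that. The trial compares standard care with standard care plus the panel, and the swab is common to both arms. The comparison stays unbiased for added value, and a smaller effect where standard care already supplies the answer is part of that question.

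**A reader might infer that these are pre-randomisation treatment events.** Only the result is shown to come first. Sampling follows as soon as possible and samples go at once to the laboratory, so many treatment decisions may fall after receipt, at an ordinary positive time. The gap concerns those that do not.

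**A reader might infer a definite loss of power.** The 40% refers to current standard-of-care methods, which include SARS-CoV-2 and influenza PCR, so Case A is a fair reading and planned power is then intact. Nor does every positive become an event: {18a} requires adjudicated relevance plus a qualifying treatment decision.

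**The analysis text is not closed.** The covariate list uses the word including, {20b} plans interactions by bacterial and viral aetiology, and an analysis plan not shown may say more. That softens the covariate point. But those subgroups rest on detected aetiology, which may include results obtained after randomisation, so they do not replace a baseline covariate. The scoring point concerns the primary outcome definition itself, which the protocol does set.

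**A tempting remedy would do harm.** Counting only treatment linked to results reported after randomisation could credit the panel, with results at about 2 h, for re-detecting a virus already known, while controls wait up to 48 h for the in-house PCR.

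**Conclusion.** The point holds as one of efficiency and definition. A result normally available before randomisation can generate primary events in both arms, it is not a named covariate, and treatment directed before sample receipt has no scoring rule.

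The size depends on an unknown share. At an assumed 10% to 20%, using the rapid result changes power from about 81% to at most 87% to 93% if the planned rates already include these events. The gain is smaller, to about 83% to 86%, if only 80% of positives have the event. If the events are additional, it changes power from about 71% to 60% up to at most 76% to 70%. Adjustment helps in every case worked, but none of these figures is a forecast for this trial.

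**What to change.** 1. Name the pre-randomisation rapid result (positive or negative) as a covariate or stratum in both primary models, beside age and sex. Use a stratified or standardised estimate. If nearly all positives have the event, use penalised fitting, because an ordinary logistic model would then run into separation.
2. State one rule for scoring treatment already directed before sample receipt, for both the binary and the time outcome. Make it the same in both arms and set it without reference to allocation.
3. Report a sensitivity analysis in rapid-test-negative patients. Keep the all-events intention-to-treat outcome as primary.

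**Cost:** a few sentences of analysis wording. The rapid result must be available to the analysis with its timing; the listed exploratory timings cover swab sampling, so capture of the result time should be confirmed. The adjusted effect is conditional on the rapid result unless it is standardised.
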